## Abstract

**Background:**

Approximately 60% of patients with advanced cancer experience the distress of cancer-related fatigue (CRF), which significantly worsens their daily function and quality of life. Baduanjin has been regarded as a promising nonpharmacological intervention for alleviating CRF, anxiety, and depression and improving quality of life. Owing to varying degrees of CRF in patients with advanced cancer, patients may have insufficient endurance, making it difficult to implement standing Baduanjin. However, relevant evidence on sitting Baduanjin for CRF in patients with advanced cancer is lacking.

**Objective:**

This study aims to design a sitting Baduanjin intervention and explore the efficacy and safety of sitting Baduanjin in reducing CRF among patients with advanced cancer.

**Methods:**

This study will be a single-blind pilot randomized controlled trial. Patients with CRF will be enlisted from a tertiary cancer hospital in China. The participants (N=98) will be randomly assigned to either a sitting Baduanjin group or a control group at a 1:1 ratio using a block-randomized scheme. The participants in the sitting Baduanjin group will undergo a 16-week sitting Baduanjin intervention in addition to standard care, whereas the participants in the control group will receive standard care in the form of a booklet on the self-management of cancer symptoms. CRF will constitute the primary outcome, whereas anxiety, depression, and quality of life will serve as the secondary outcomes. These outcomes will be assessed at baseline (T0), 12 weeks (T1), and 16 weeks (T2).

**Results:**

The study was approved by the Medical Ethics Review Committee of Hunan Cancer Hospital in March 2024 (ethics approval number 2024.50). Before this full-scale randomized controlled trial, we conducted a pilot study, which demonstrated the feasibility and acceptability of sitting Baduanjin for patients with advanced cancer, with potential benefits for relieving fatigue.

**Conclusions:**

This randomized trial will evaluate the effectiveness of sitting Baduanjin exercises in alleviating CRF among patients with advanced cancer. If proven effective, it will provide a promising alternative intervention for patients with advanced cancer.

## Introduction

Cancer-related fatigue (CRF) is a distressing, lasting, subjective state of physical, emotional, and/or cognitive tiredness that is not in proportion to recent activities. It is related to cancer or associated treatments and is frequently accompanied by dysfunction [1]. Approximately 60% of patients in the advanced stage of cancer experience CRF [2]. CRF is one of the most prevalent symptoms manifested by patients with advanced cancer, and it can considerably deteriorate their quality of life and daily functioning [3]. Furthermore, it constitutes one of the primary reasons for the disruption of treatment or the deterioration of the disease [4]. Therefore, relieving CRF for patients with advanced cancer is critical.

At present, there is no acknowledged standard for the treatment of CRF [5] as its pathogenesis remains unclear. It could be associated with proinflammatory cytokines, growth factors, modulation of the circadian rhythm, disruption of the adrenal axis, serotonin imbalance, afferent activation of the vagus nerve, or the generation or use of abnormal adenosine triphosphate [6]. Previous research has shown that aerobic exercise (including tai chi and yoga) might be an effective CRF intervention and prove to be more efficacious than existing pharmaceutical treatments in alleviating CRF [7,8]. The current guidelines for the treatment of CRF recommend exercise-based activities rather than pharmaceutical interventions [9]. Aerobic exercise mitigates CRF both during and after treatment, particularly for those with solid tumors [10], and contributes to alleviating the cognitive and physiological consequences of fatigue [11]. Despite the existing evidence on the positive effects of aerobic exercise, many patients with advanced cancer cannot adhere to or perform exercise while standing due to weakness [12]. Therefore, it is necessary to find an appropriate exercise for those patients with advanced cancer who need to exercise while sitting.

Baduanjin, a traditional Chinese mind-body workout consisting of just 8 simple movements, is a proper moderate-intensity exercise for CRF in the treatment of advanced cancer as it is easy to master, consumes less energy, and requires no specific equipment [13]. Previous research indicates that Baduanjin is capable of alleviating the fatigue symptoms of patients with diverse diseases [14,15]. From the viewpoint of traditional Chinese medicine, CRF belongs to the category of deficiency and is marked by insufficient visceral functions and deficiencies in *qi*, blood, *yin*, and *yang*. Baduanjin can relieve CRF by facilitating the smooth flow of meridians, enhancing *qi*, improving blood circulation, regulating internal organ functions, boosting the immune system, and eliminating harmful toxins [16,17].

However, the current research on Baduanjin for patients with advanced cancer mainly focuses on standing Baduanjin. Due to varying degrees of CRF in patients with advanced cancer, patients may have insufficient endurance, making it difficult to implement standing Baduanjin. Therefore, sitting Baduanjin is more suitable for these patients. Currently, there is little research on sitting Baduanjin. One study developed a sitting Baduanjin intervention for patients with sepsis undergoing noninvasive ventilation [18]. The findings suggest that sitting Baduanjin could improve patients’ muscle strength and activities of daily living [18]. Another study developed a sitting Baduanjin intervention for older adults and found that it improved their balance and motor function [19]. Previously, the evidence on the benefits of Baduanjin mainly came from studies on patients with breast cancer and other populations. Before this trial, the efficacy of Baduanjin in relieving fatigue in patients with advanced cancer had not been confirmed. Due to the differences in symptom burden, there is currently no direct empirical verification of the impact of the previously developed sitting Baduanjin interventions on patients with advanced cancer. This emphasizes a significant need to investigate the effects of performing sitting Baduanjin on CRF in patients with advanced cancer.

## Methods

### Study Design

This research is a single-blinded, parallel randomized controlled trial (RCT) with 2 arms. An overall diagram of the research is presented in Figure 1. The schedule of the study adheres to the SPIRIT (Standard Protocol Items: Recommendations for Interventional Trials) guidelines [20].

**Figure 1. F1:**
[figure not shown]
CONSORT (Consolidated Standards of Reporting Trials) flow diagram of the study.

### Study Setting and Participants

Participants will be enlisted from a tertiary cancer hospital in Hunan, China. Patients with cancer will be eligible for enlistment if they meet the following criteria: (1) diagnosis of stage III or IV cancer; (2) age of >18 years; (3) being informed of their illness; (4) capability of communicating and understanding the research; (5) willingness and ability to provide written informed consent for study participation; and (6) Revised Piper Fatigue Scale (RPFS) score of ≥4, indicating moderate to severe fatigue. Patients will be excluded in case they meet any of the following exclusion criteria: (1) currently using medications for fatigue, sleep disturbance, or depression, such as antidepressants, psychostimulants, or hypnotics; (2) being too frail to participate in physical activities due to terminal stages of chronic illnesses or having cognitive impairment and/or severe mental illness; (3) having serious exercise contraindications, such as cardiovascular or joint problems; and (4) participating in other exercise research programs.

### Sample Size Calculation

The sample size was computed using the G*Power software (version 3.10). No previous research reports have emerged regarding the effect of sitting Baduanjin on CRF in patients with advanced cancer. Therefore, the effect value was set to 0.50. In the G*Power software, the *t* test for the mean difference between 2 independent samples was selected. With an effect size of 0.69 [21], a statistical power of 0.85, and a 2-tailed test, the sample size for each group was calculated to be 39. Thus, considering a conservative anticipation of a 20% dropout rate, the final sample size will be 49 in each group, with a total of 98 participants.

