## Results

The study was approved by the Medical Ethics Review Committee of Hunan Cancer Hospital in March 2024 (ethics approval number 2024.50). Before this full-scale RCT, we conducted a pilot study. A total of 24 participants were recruited between March 2025 and April 2025. After the intervention, 18 participants, comprising 9 from the intervention group and 9 from the control group, completed the follow-up evaluation. The retention rate was 75%. The pilot study demonstrated the feasibility and acceptability of sitting Baduanjin for patients with advanced cancer, with potential benefits for relieving fatigue.

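### The sample size section names two design effects, 0.50 and 0.69, without reconciling them; N=98 and the 85% power follow only from 0.69, and power at 0.50 is about 59%

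*Protocol article*

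**What the plan says.** All the statements at issue are in one paragraph of the protocol article, Methods, Sample Size Calculation.

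- On prior evidence: "No previous research reports have emerged regarding the effect of sitting Baduanjin on CRF in patients with advanced cancer".
- The conclusion drawn from this: "Therefore, the effect value was set to 0.50".
- After naming a t test for two independent means, the inputs used: "With an effect size of 0.69 [21], a statistical power of 0.85, and a 2-tailed test".
- The result: 39 per group, raised to 49 per group and 98 in total for 20% dropout.

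The Introduction adds: "Before this trial, the efficacy of Baduanjin in relieving fatigue in patients with advanced cancer had not been confirmed". Alpha is not given in the sample size paragraph; Data Analysis sets significance at P below .05.

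**The concern.** The word that opens the 0.50 sentence presents that value as a consequence of having no direct data. The calculation then uses a larger value from a cited source. The text does not say that 0.50 was a fallback, that it was superseded, or that it describes a different quantity. These are two current statements about the same design input.

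The choice matters because the required sample size varies with the inverse square of the effect. A reader who takes 0.50 as the design effect will attach the 85% power to it, and that power does not hold there. The trial would then be judged, when its results are read, against an ability to detect a moderate effect that it was not sized to have.

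**Working it through.** **Inputs.** From Sample Size Calculation: two-sample t test, two-tailed, power 0.85, effect 0.50 or 0.69, 39 per group, 20% dropout, 49 per group. From Randomization and Allocation Concealment: 1:1 allocation. From Data Analysis: alpha 0.05, taken as two-sided. No SD is given, so effects are in SD units.

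**Formula.** For n per group and standardised effect d, the test has 2n − 2 degrees of freedom and noncentrality d × √(n/2). Power is the probability that a noncentral t variable with these parameters falls beyond the two-sided 5% critical values. Dropout inflation is n / (1 − 0.20).

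**Step 1: reproduce the plan's figure with d = 0.69.**
- Power 0.85 needs n = 38.7, so 39 per group (normal approximation: 38).
- At n = 39 the noncentrality is 0.69 × √19.5 = 3.05, and power is 0.853.
- 39 / 0.80 = 48.75, so 49 per group and 98 in total.

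This matches the protocol exactly. It also supports the alpha of 0.05 taken from Data Analysis.

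**Step 2: the same test with d = 0.50.**
- At n = 39 the noncentrality is 0.50 × √19.5 = 2.21, and power is 0.587 (normal approximation 0.598).
- At n = 49, with nobody lost, the noncentrality is 0.50 × √24.5 = 2.47, and power is 0.688 (normal approximation 0.697).
- Power 0.85 needs n = 72.8, so 73 evaluable per group; 73 / 0.80 = 91.25, so 92 per group and 184 in total.

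**Step 3: smallest effect detectable with 85% power.** About 0.69 with 39 per group and about 0.61 with 49 per group. Both are above 0.50.

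**Step 4: could another reading rescue 0.50?** A one-sided 5% test, which contradicts the stated two-tailed test, gives 0.707 at n = 39 and 0.792 at n = 49. Neither reaches 0.85.

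| Effect | Power, 39 per group | Power, 49 per group | Evaluable per group for 85% | Total after 20% dropout |
|---|---|---|---|---|
| 0.69 | 0.853 | 0.922 | 39 | 98 |
| 0.50 | 0.587 | 0.688 | 73 | 184 |

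**The case against.** **The protocol attaches its 85% power to 0.69, and there it is correct.** This stands. A reader might infer that the calculation is wrong or that the stated power is false. The documents do not support that: they nowhere claim 85% power at 0.50, and the 0.50 sentence may simply be left over. The defect is an unreconciled inconsistency. It still needs correcting, because the text gives no way to tell which sentence is the leftover.

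**The planned analysis is a repeated-measures GEE, which may have more power than the t test.** This is fair as a limit on the 59%. As an illustration only, suppose the analysis adjusted for baseline with baseline–outcome correlation r. The effective effect would be 0.50 / √(1 − r²). With 39 per group, power would be about 0.63, 0.71 or 0.86 for r = 0.3, 0.5 or 0.7. Matching 0.69 needs r of about √(1 − (0.50/0.69)²) = 0.69. The article states no baseline adjustment and no correlation, and it claims no such gain. Its 85% rests on the unadjusted t test, so the comparison at 0.50 belongs on the same footing.

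**The cited source for 0.69 may be close to this setting.** A reader might infer that 0.69 comes from a different patient population. The documents do not go that far. By the protocol's own statement, the source cannot be sitting Baduanjin for fatigue in advanced cancer. But the Introduction says that Baduanjin research in advanced cancer has mainly used the standing form, so the source could concern the same population. Whether 0.69 is too optimistic is a judgement that the documents do not settle.

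**Two further inferences go too far.** One is that a non-significant result could never exclude an effect of 0.50. With 39 per group the 95% half-width is about 0.45 SD, so an observed difference below about 0.05 SD would exclude it; what a null result excludes depends on the interval obtained. The other is that the two effect sizes reflect doubt over whether this is a pilot. The Abstract does say "This study will be a single-blind pilot randomized controlled trial" and the Results say "Before this full-scale RCT, we conducted a pilot study", but nothing links that labelling to the effect size. It is a separate matter.

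**Conclusion.** The concern holds as an internal contradiction about the effect behind the primary power claim. The paragraph sets 0.50 and computes from 0.69, and only 0.69 yields 39, 49 and 98 with 85% power. At 0.50 the sizing test has about 59% power with 39 evaluable per group and about 69% with all 49; 85% would need 184 participants.

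These figures assume two-sided alpha 0.05, 1:1 allocation and an unadjusted comparison of two means at one time point. They do not give the power of the GEE, which cannot be computed from the article. They do not show that 98 is the wrong number to recruit. They show that the article must say which effect that number serves.

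**What to change.** Keep N=98. State one design effect in Sample Size Calculation and justify it.

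- **If 0.69 is kept:** delete the 0.50 sentence. Say that 0.69 does not come from sitting Baduanjin for fatigue in advanced cancer, as the protocol's own statement implies, and why it is thought to apply. Report beside it that power at 0.50 is about 59% with 39 evaluable per group.
- **If 0.50 is kept:** remove 0.69 as the design value and replace the 85% with about 59% at 39 evaluable per group. The 85% and N=98 cannot both stand with 0.50.

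Either way, state alpha in the same paragraph so that the calculation can be reproduced from it. The change is wording only and adds no patients. The cost is that the stated power looks less favourable.

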### Recruitment

Patients with advanced cancer will be approached and recruited in a tertiary cancer hospital by a research nurse. This research nurse will screen patients with advanced cancer according to the inclusion and exclusion criteria. Information on this study, encompassing the purpose, the intervention, and the possible benefits and harms, will then be offered to the potential participants to obtain their informed consent. In addition, recruitment posters will be displayed in the study hospital to expand recruitment. After the participants’ consent is obtained, the researchers will invite the participants to provide baseline data using paper questionnaires.

### Randomization and Allocation Concealment

The participants will be randomly allocated into 2 groups in a 1:1 ratio using a block-randomized scheme with block sizes of 4 or 6. One set of randomization sequences will be generated through an online randomizer [22] based on the estimated sample size. To guarantee allocation concealment, the randomization sequences will be produced by a research assistant who will not be involved in any other part of this study. The randomization sequences will then be put into sequential, sealed, opaque envelopes and kept by another research assistant who is not involved in the study. The randomization sequences will be inaccessible to other research staff. Once an eligible participant gives consent to take part in the study and finishes the baseline assessment, the research nurse in charge of recruitment will call the research assistant to disclose the allocation result.

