### Data Collection

The baseline assessments will be conducted by the research nurse who is in charge of participant recruitment and random assignment to groups. All participants will be requested to complete the RPFS, GAD-7, PHQ-9, FACT-G, and demographic data sheet on-site at baseline (T0). The reassessment of the outcomes will be conducted at 12 (T1) and 16 (T2) weeks after baseline. Follow-up data will be gathered via telephone by a research assistant who will be blinded to the participants’ group allocation. The schedule of study outcome assessments is outlined in Table 2.

**Table 2. T2:** SPIRIT (Standard Protocol Items: Recommendations for Interventional Trials) diagram of enrollment, treatment, and assessments over the intervention period.

	Study period					
	Enrollment	Baseline assessment	Allocation	Intervention week 12 (T1)	Intervention week 16 (T2)	
Recruitment						
Eligibility screen	✓					
Informed consent	✓					
Randomization						
Allocation			✓			
Interventions						
Experimental group						
Control group						
Patient-reported outcomes						
Demographic characteristics		✓				
RPFS^a^		✓		✓	✓	
GAD-7^b^		✓		✓	✓	
PHQ-9^c^		✓		✓	✓	
FACT-G^d^		✓		✓	✓	
Adverse effects or events				✓	✓	
Adherence to exercise						

a RPFS: Revised Piper Fatigue Scale.

b GAD-7: 7-item Generalized Anxiety Disorder Scale.

c PHQ-9: Patient Health Questionnaire–9.

d FACT-G: Functional Assessment of Cancer Therapy–General.

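### The nurse who recruits, screens and takes baseline data also learns every allocation, so a running tally predicts the next arm about 69% of the time and leaves room for selective enrolment

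*Protocol article*

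**What the plan says.** All references are to the Protocol article.

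- **Recruitment:** "Patients with advanced cancer will be approached and recruited in a tertiary cancer hospital by a research nurse". The next sentence gives the same person the eligibility check: "This research nurse will screen patients with advanced cancer according to the inclusion and exclusion criteria".
- **Study Setting and Participants:** one hospital. Among the exclusions is "being too frail to participate in physical activities due to terminal stages of chronic illnesses", with no score or threshold attached.
- **Data Collection:** baseline assessments are done by "the research nurse who is in charge of participant recruitment and random assignment to groups".
- **Randomization and Allocation Concealment:** 1:1 allocation by a "block-randomized scheme with block sizes of 4 or 6", from one set of sequences, with no stratification factor named. One assistant generates the sequence. Another keeps the sequential, sealed, opaque envelopes. Once consent and baseline are complete, "the research nurse in charge of recruitment will call the research assistant to disclose the allocation result". The section presents these steps as guaranteeing concealment.
- **Blinding:** participants and investigators are not blinded; outcome assessors are.

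**The concern.** Sealed envelopes conceal the next assignment only if the assignments already revealed do not give it away. Here one role sees every past result, in order, from a list that returns to balance every 4 or 6 patients. That same role decides whom to approach and when, and applies an exclusion that calls for judgement.

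A nurse who expects the next slot to be the exercise arm could, without intending it, delay or exclude a patient who seems unlikely to manage the exercise. This would make the arms differ before randomization. Analysis by intention to treat does not remove such a difference, because it keeps patients in the arm they were given and cannot undo how they were chosen for it.

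**Working it through.** **Inputs.** N = 98, 1:1, blocks of 4 or 6, one list (Sample Size Calculation; Randomization and Allocation Concealment). The article does not say how the two sizes are ordered, so I assume an equal random mix and also show each size alone.

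**The plan's own figures.** The randomization section gives no number beyond the ratio and block sizes. The sample size reproduces: d = 0.69, two-sided alpha 0.05 and 39 per group give power 0.853 by the noncentral t. Then 39 / 0.80 = 48.75, rounded up to 49 per group, 98 in total.

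**Correct guesses from a running tally.** The guesser picks the arm that is behind and tosses a coin when the arms are level. Every completed block is balanced, so the overall tally equals the tally within the current block, and the guesser need not know where blocks begin or how long they are. In a block of 2m, m steps move towards balance and all are guessed correctly. Each time the arms are level, the coin toss adds half a correct guess. The expected number of level points before the block ends is 2^(2m)/C(2m,m) − 1, so

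expected correct = m + [2^(2m)/C(2m,m) − 1]/2.

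| Block | Expected correct | Share |
|---|---|---|
| 4 | 2 + (16/6 − 1)/2 = 2.83 | 70.8% |
| 6 | 3 + (64/20 − 1)/2 = 4.10 | 68.3% |
| Equal mix of 4 and 6 | (2.83 + 4.10)/10 | 69.3% |
| 8 | 4 + (256/70 − 1)/2 = 5.33 | 66.6% |
| 10 | 5 + (1024/252 − 1)/2 = 6.53 | 65.3% |

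Simulation of 2,000 lists of 98 with mixed blocks gives 69.2%, about 68 correct against 49 by chance, an excess of about 19. A guesser who also knows the possible sizes and updates by Bayes' rule is right equally often (69.2%).

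**Assignments known with certainty.** In the same simulation, a guesser who knows the possible sizes, but not the length of the current block, is certain of about 5.4 of 98 assignments, or 6%. The same guesser can call about 49% with at least 75% confidence. If the current block length is known, the expected number certain is 2m/(m + 1) per block: 4/3 of 4 (33%) and 3/2 of 6 (25%), or (4/3 + 3/2)/10 = 28% for the mix.

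**What acting on the guess could do.** The article gives no measure of selection, so this is an assumed range. Suppose the enrolled patient's expected outcome is shifted by η SD in the direction of the guessed arm, and by nothing when the arms are level. The bias in the difference between arms is then about 2η(2 × 0.692 − 1) = 0.77η. The false-positive rate uses a two-sided t test with 39 per group and noncentrality bias × √(39/2).

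| η (SD, assumed) | Bias (SD) | False-positive rate (nominal 5%) |
|---|---|---|
| 0.1 | 0.08 | 6% |
| 0.2 | 0.15 | 10% |
| 0.3 | 0.23 | 17% |

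**The case against.** The plan has standard safeguards: independent sequence generation, envelopes held by someone else, more than one block size, and disclosure only after consent and baseline. Recruitment posters mean the nurse does not originate every contact. The stage criterion and the fatigue-score threshold leave little discretion, and the frailty exclusion is tied to terminal stages of chronic illness. Baseline fatigue is recorded before allocation, so selection on it would be partly visible. Nothing in the article shows that any recruiter would select. All of this stands and limits how serious the point is. It does not answer it, because the safeguards act on the current envelope, whereas inference about the next patient acts earlier, at approach, timing and screening.

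A reader might infer more than the article supports:

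- **That over a quarter of assignments are fully determined.** The 28% needs knowledge of the current block length. Under a random mix the figure is about 6%.
- **That printing the block sizes causes the problem.** Knowing them hardly changes the 69%, which comes from the tally alone.
- **That the Blinding section is contradicted.** The nurse does not know a participant's arm when taking that participant's baseline, and follow-up is assigned to a blinded assistant.
- **That the nurse controls the sequence.** The Data Collection wording can be read as making the telephone call. It is loose, and at odds with the separation of roles described under randomization, but the list and envelopes are held elsewhere.
- **That the nurse takes consent.** Recruitment implies this only; information "will then be offered to the potential participants to obtain their informed consent", in the passive voice.

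**Conclusion.** The point holds as a risk of selection bias. One role recruits, screens, takes baseline data and hears each result, and a simple tally predicts the next arm about 69% of the time (68% to 71% across the possible block patterns) instead of 50%. The claim of guaranteed concealment is stronger than the procedure delivers.

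This rests on a single list without strata, as the article describes it, and on the recruiting nurse hearing every allocation, as it states. It does not show that bias will occur: the 0.08 to 0.23 SD and the 6% to 17% false-positive rates follow only from assumed selection of 0.1 to 0.3 SD. The change is worth making because it costs almost nothing.

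**What to change.** 1. Once eligibility and the T0 assessment are signed off, have the envelope holder disclose each result, for both arms, to existing staff who do not screen, enrol or assess outcomes. If this is the nurse who runs the week 1 training, state that this is a different person from the recruiting nurse, since the Experimental Group section does not say so. Also state how control allocations reach that person, because controls have no such session.
2. Keep block sizes out of documents available to recruiters. This is good practice but hardly lowers the 69%.
3. Reword Data Collection so that the recruiting nurse is not described as responsible for random assignment, in line with Randomization and Allocation Concealment.

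The cost is a changed call route and a wording correction; the sample size stays at 98. The recruiter may still learn some allocations informally, so the risk is reduced and not removed.

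Larger variable blocks are optional. A mix of 8 and 10 gives (5.33 + 6.53)/18 = 65.9% correct guesses, a gain of only about 3 percentage points. Unrestricted randomization would bring guessing down to 50%, but at N = 98 the arms would differ by about 8 patients on average (√98 × 0.80 = 7.9), so it is a trade-off.
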